### Allocation

This study aims to recruit an equal number of parent and adolescent users. Parent and adolescent participants are randomized to the intervention and control groups using a 1:1 ratio. Parent and adolescent participants are stratified into 2 subgroups: those who smoke traditional combustible cigarettes (with or without e-cigarette use) and those who report exclusive use of e-cigarettes. A computer-generated randomization list created by a biostatistician external to the study team is used to randomize participants within each group.

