## Introduction

Tobacco use is the single greatest preventable cause of morbidity and mortality in Canada, accounting for 48,000 deaths and CAD $16.2 billion (US $11.9 billion) in attributable health-related costs annually [1,2]. Smoking is a significant risk factor for multiple cancers [3] as well as cardiovascular diseases [4], thus shortening the life expectancy of smokers who initiate during adolescence by more than 10 years [4]. Despite parental smoking being an important risk factor for child initiation of tobacco (children of parents who smoke have 4-fold greater odds of becoming smokers when compared with children of nonsmoking parents) as well as for the development of several illnesses, such as bronchiolitis, asthma exacerbations, and pneumonia [5], about 15% of Canadian children are still exposed to household secondhand smoke [6]. Parents are thus an important target for smoking cessation interventions to improve their own health and protect that of their children and future generations. Given that 90% of smokers start smoking before the age of 18 years [7], adolescence represents a critical period to intervene in the fight against smoking [8].

Smoking among adolescents and young adults remains common despite rates decreasing over the past 3 decades, and adolescent use of nicotine-containing e-cigarettes (hereafter referred to as e-cigarettes) has shown a worrying increase over the past 10 years [9]. Most adults who use e-cigarettes (e-cigarette use is referred to interchangeably with vaping) do not have a history of tobacco use; however, once vaping has been initiated, the risk of subsequent tobacco, alcohol, and drug use increases [9]. Commonly used e-cigarettes usually contain high concentrations of nicotine, and while potentially effective for adult smoking cessation [10], they are not effective for youth smoking cessation and should not be recommended in this population [11].

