### Recruitment

The appointment schedules of participating clinics will be reviewed the week before by the research team, and a recruitment schedule will be made according to the clinical volume of each clinic to maximize the number of potential patients approached. At the time of registration for their scheduled appointment, parents or legal guardians (hereafter referred to as parents) of children aged between 0 and 17 years as well as adolescents aged between 14 and 17 years are approached by a research assistant in the clinic waiting room to complete the screening survey on an electronic tablet. The survey is preceded by an abbreviated consent form. This approach is similar to that which was successfully used in CEASE studies in pediatric primary care in the United States [23]. Parents and adolescents are asked sociodemographic, smoking, and e-cigarette screening questions (see “Inclusion and Exclusion Criteria” section). Participants who respond “yes” to at least 1 of the 2 screening questions are invited to participate in the CEASE pilot study and have access to the full consent form. These forms are available in the Multimedia Appendix 1. During the entire study period, research assistants keep a detailed recruitment log, including information on participant screening, eligibility, recruitment, randomization, and retention in the study.

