### Inclusion and Exclusion Criteria

#### Inclusion Criteria

Parents of children aged between 0 and 17 years who smoke cigarettes or use nicotine-containing e-cigarettes. Users are defined as those who answer “yes” to at least 1 of the 2 screening questions: (1) Have you smoked a single cigarette, even a puff, in the past 7 days? (smoking), and (2) Have you used an e-cigarette or vaping device containing nicotine, even a puff, in the past 7 days? (vaping).

Parents are eligible if (1) they are aged 18 years or older, (2) their child is aged between 0 and 17 years, (3) they are attending a regular scheduled medical appointment, and (4) they are sufficiently proficient in either French or English to be able to read and answer a written questionnaire. Informed consent is obtained before data collection.

Adolescent users are defined as those who answer “yes” to at least 1 of the above screening questions.

Adolescents are eligible if they are aged between 14 and 17 years, meet the aforementioned 3rd and 4th criteria, and have provided informed consent (in Québec, adolescents aged 14 years can provide consent).

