### Strengths and Limitations

This study includes several strengths. First, it builds on the CEASE intervention, which has previously been demonstrated to be effective and cost-effective. Second, the electronic format of the screening and intervention will facilitate the integration of the tool in clinic workflow without any required intervention from clinical staff and will help with scale-up to additional sites. Finally, the study leverages existing cigarette and e-cigarette cessation resources, foregoing the need for additional costs for resource development. This also means that those resources can evolve and improve over time without affecting the design or feasibility of the study.

This study has certain limitations. Given the pilot nature of the study and the small sample size, this study does not have the statistical power to evaluate the effectiveness of the CEASE intervention. This study is also being conducted exclusively in an urban tertiary care hospital, which may not be reflective of pediatric clinics in community hospitals or other primary care clinics. Nonetheless, as recruitment is taking place in both general pediatric and adolescent medicine clinics as well as several specialized pediatric clinics, it allows for testing of the CEASE model in a diverse parent and adolescent patient group. Given this diversity of participants and recruitment clinics within a single center, we elected to randomize at the participant level rather than following the cluster-randomization protocol previously used to evaluate CEASE [23]. This decision does, however, pose a risk of contamination, wherein participants in the control group learn of the intervention and choose to seek out these publicly available smoking cessation resources themselves. While this may result in a decreased effect size of “The Clinical Effort Against Secondhand Smoke Exposure–Canada” (CanCEASE) in this study, all participants are offered access to these resources at the end of the study period, and the CanCEASE questionnaire itself may prompt individuals wishing to quit smoking or vaping to seek out these publicly available resources themselves during the study. Furthermore, cluster randomization would have been impractical in the context of this pilot study, as a larger sample size is required.

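### A parent and an adolescent from one family can both enrol and are randomized separately, so about half of any such pairs are split between arms and the control member may meet CEASE materials through a relative

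*Protocol article*

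**What the plan says.** Parents qualify if, among other criteria, "their child is aged between 0 and 17 years" (Inclusion Criteria), which takes in the parents of 14- to 17-year-olds. For the younger group, "Adolescents are eligible if they are aged between 14 and 17 years, meet the aforementioned 3rd and 4th criteria", and they must give consent. Recruitment has parents approached at registration, and likewise "adolescents aged between 14 and 17 years are approached by a research assistant in the clinic waiting room". The Exclusion Criteria cover only parental objection and urgent visits, and they foresee that a parent may be there with the adolescent. No criterion concerns a second member of the same family.

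On allocation, "Parent and adolescent participants are randomized to the intervention and control groups using a 1:1 ratio", each age group is split by product used, and "A computer-generated randomization list created by a biostatistician external to the study team is used to randomize participants within each group". Strengths and Limitations confirms the unit: "we elected to randomize at the participant level rather than following the cluster-randomization protocol previously used to evaluate CEASE". It adds: "This decision does, however, pose a risk of contamination, wherein participants in the control group learn of the intervention". It says this may reduce the effect size and that cluster randomization would have needed a larger sample. Families are not mentioned there.

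A CEASE participant receives a printed and emailed NRT recommendation, can sign up for behavioral support on the tablet, gets an email or SMS reminder in the following week, and is offered the resources again at 1, 3 and 6 months.

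**The concern.** A family pair split between arms links a control participant closely to someone who holds the intervention's materials. Participants are not blinded and the behavioral resources are public, so the control member could act on what the relative brings home. Use of cessation resources, motivation to quit and cessation are the very endpoints that the Analyses section compares between arms, and contamination would pull each of them toward no difference.

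The reason given for not clustering, sample size, applies to clinics as clusters. It hardly applies to families, where a cluster would usually be two people. The pilot is meant to inform a full-scale trial, so how often relatives co-enrol and are split is design information that it should supply. As described, that may not be recoverable: contact identifiers are limited to email and phone, participants carry individual codes, and no family link is mentioned.

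**Working it through.** The article states no figure for family pairs or for contamination, so there is nothing of its own to reproduce.

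**Inputs from the article**
- Allocation probability 0.5 per person (Allocation).
- Target of 50 parents and 50 adolescents, hence about 100 × 0.5 = 50 controls.
- 15% combined use of cigarettes and vaping devices, in parents and in adolescents (Power Calculations).
- An odds ratio of 4 between parental and child smoking: "children of parents who smoke have 4-fold greater odds of becoming smokers when compared with children of nonsmoking parents" (Introduction).

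**Inputs that are assumptions**
- Every user in the parent group's population is equally likely to be an adolescent's parent, except as the odds ratio modifies it.
- The using parent of an enrolled adolescent attends and enrols with probability 20% to 100%.

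**Step 1: chance of a split.** A parent and an adolescent are always in different randomization groups, so I take their allocations as independent. P(opposite arms) = 2 × 0.5 × 0.5 = 0.50.

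**Step 2: effect of m pairs.** Expected opposite-arm pairs = m/2, each containing one control. P(at least one) = 1 − 0.5^m.

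| Pairs (m) | Expected opposite-arm pairs | Share of 50 controls | P(at least one) |
|---|---|---|---|
| 0 | 0 | 0% | 0 |
| 2 | 1.0 | 2% | 0.75 |
| 5 | 2.5 | 5% | 0.97 |
| 10 | 5.0 | 10% | >0.99 |

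**Step 3: how many pairs, with no family association.** If 15% of adolescent users have a using parent: 50 × 0.15 = 7.5. With 20% to 100% of those parents enrolling, there are 1.5 to 7.5 pairs and 0.75 to 3.75 affected controls (1.5% to 7.5% of 50).

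**Step 4: how many pairs, with the fourfold odds applied to all use.** Let p be the joint probability that parent and adolescent both use, with both margins 0.15. Then p(0.70 + p)/(0.15 − p)² = 4, which gives 3p² − 1.9p + 0.09 = 0 and p = 0.0516. The conditional probability is 0.0516/0.15 = 0.344, so 50 × 0.344 = 17.2 adolescents have a using parent. With 20% to 100% enrolling, there are 3.4 to 17.2 pairs and 1.7 to 8.6 affected controls (about 3% to 17% of 50).

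**Step 5: combined range.** From 0.75 to 8.6, that is roughly 1 to 9 of about 50 controls. If every affected control behaved exactly like a CEASE participant, the between-arm difference would shrink by that same share, at most about 17%. Partial exposure shrinks it less.

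**Step 6: cost of keeping pairs together.** With 17 pairs, 34 of 100 participants are in clusters of two, so the pooled design effect is about 1 + 0.34 × ICC, or 1.07 at an assumed ICC of 0.2. Within the parent or adolescent groups a pair contributes one person to each, so it adds no clustering there.

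**The case against.** The strongest reply is that this rests on silence in a condensed article. A rule on co-enrolment may be in the full protocol, and the authors have disclosed and reasoned their choice of individual randomization, contamination included. The primary outcome cannot be affected, the between-arm comparisons are exploratory and admittedly underpowered, and no decision rule uses them. Enrolment had also passed its target, with 115 recruited by 30 September 2023 (Results). All of this limits the weight of the point. It does not remove it: the article describes eligibility and allocation in detail, these provisions allow split families, and the general disclosure neither names that route nor gives a reason that fits it.

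Three stronger readings are not supported:
- A reader might infer that the control member is directly exposed to CEASE. The documents give that person no motivational module, no sign-up and no NRT recommendation of their own. Any contact is second-hand.
- A reader might infer from the fourfold odds that such pairs will be common. That figure concerns smoking, while Power Calculations puts vaping at 18% and smoking at 4% among 15- to 17-year-olds in Quebec. The article also does not say that both members of a family are approached at one visit, and it plans on 50% screened and 20% enrolled.
- A reader might argue that correlation within split pairs harms the comparison. In a pooled analysis, positively correlated people in opposite arms do not inflate the variance of the difference; pairs in the same arm do, slightly.

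**Conclusion.** The point holds in a limited form. On the text shown, a parent and an adolescent from one family can both enrol, and half of any such pairs are expected to be split between arms. That half follows from separate 1:1 allocation and needs no further assumption about prevalence.

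The number of pairs cannot be derived from the article. The figure of roughly 1 to 9 affected controls is a range under assumptions. Its lower end ignores family association and has 20% of using parents enrolling; its upper end needs all of them to enrol and the smoking odds ratio to cover vaping. The harm is dilution of exploratory signals on resource use, motivation and cessation, with no effect on the recruitment-rate outcome. It is worth correcting because it is cheap to do so and because those signals, and the frequency of co-enrolment itself, feed the design of the next trial.

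**What to change.** Add to Allocation:
- When two eligible members of one family present together, screen and consent both before any allocation, then randomize the pair as one unit to the same arm. Allocating the first and then giving the second the same arm is not equivalent: research assistants are unblinded (Blinding), so they would know the second member's arm before enrolment.
- A relative who enrols at a later visit cannot be fully concealed under a same-arm rule, so that person should only be linked and reported.

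Add to the recruitment log and Analyses:
- A family link code, which needs no name, address or date of birth.
- The number of linked pairs and of opposite-arm pairs, including those already enrolled where they can be identified.
- A sensitivity analysis of the exploratory between-arm comparisons that leaves out opposite-arm pairs.

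The costs are a slight departure from 1:1 balance within strata, a few correlated same-arm pairs in pooled comparisons, and one more log field. Because recruitment was already past target, the allocation rule mainly serves any remaining enrolment and the full-scale trial; linking and reporting can still be useful in this one.

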### Blinding

This is a single-blinded study in which investigators will be blinded to the participant’s group allocation, and data analysis is blinded, but participants and research assistants remain unblinded. Pediatricians may decide to discuss smoking and vaping with families as part of their usual care, and participants may mention the CEASE intervention during the encounter with the provider. As such, participants and physicians will not be blinded. Participant data is anonymized using individual participant codes. No participant identifiers (eg, birth date and hospital number) are included in the database.

### Outcomes

The capacity of CEASE to provide cessation assistance for parental and adolescent smoking and e-cigarette use is assessed using a series of outcomes detailed in Tables 1 and 2. Table 1 includes all clinic-level outcomes, while Table 2 includes all patient-level outcomes. Each table includes details and a summary of each outcome measure, their operational definition, as well as the suggested time line for data collection and feasibility threshold when applicable. Outcomes were based on [name]’s previous experience conducting CEASE feasibility and effectiveness trials in the United States [23].

Feasibility thresholds of 50% of potential participants screened for eligibility, 15% clinic-level smoking and vaping prevalence, 20% enrollment rate, and 3 participants (total) recruited per week (at least 6 parents and 6 adolescents recruited per month; primary outcome for this study) have been set (Table 1). Given an average of 250 patients seen per week across all 4 clinic recruitment sites, we anticipate that these thresholds will allow for 100 participants to be recruited over 36 weeks (9 months). Similarly, a feasibility threshold for baseline and follow-up questionnaire completion has been set at 90% and 80%, respectively, as shown in Table 2.

Data are obtained directly from participants through baseline and follow-up questionnaires, as well as from recruitment logs, biochemical assay results, and key informant interviews with clinic staff (eg, clinical nurse, front desk staff, and medical director) to inform about the potential impacts of the study on clinic flow. The key informant semistructured interview template is presented in Multimedia Appendix 2.

**Table 1 table1:** Clinic-level outcomes of a pilot randomized controlled trial evaluating the feasibility and preliminary effectiveness in Canadian pediatric clinics of a brief digital screening and intervention tool for parental and adolescent tobacco and electronic cigarette use.

Outcome				Operational definition and details of measure	Timeline	Data collection	Feasibility threshold
**Recruitment**							
	Clinic flow			Number of potential participants (parent and adolescent) per month for each clinic	Throughout	Recruitment log	N/A^a^
	Proportion screened			Proportion of potential participants screened for eligibility	Throughout	Recruitment log	>50%
	Clinic-level smoking and vaping prevalence			Self-reported smoking and vaping rates among parents and adolescents screened	Throughout	Recruitment log	>15%
	Eligibility rate			Number of eligible parents and adolescents per month for each clinic	Throughout	Recruitment log	N/A
	Enrollment percentage			Proportion of eligible participants approached who are enrolled	Throughout	Recruitment log	>20%
	Reason for declining			Reasons for declining participation in the study	Throughout	Recruitment log	N/A
	Recruitment rate (primary outcome)			Total number of participants recruited per month (parents and adolescents)	Throughout	Recruitment log	>3 participants, total, per week; >6 adolescents and >6 parents per month
**Feasibility of the intervention**							
			Interest in smoking or vaping cessation	Proportion of eligible participants per category (parents and adolescents) who declare interest in smoking or vaping cessation	End of study	Baseline and follow-up questionnaires	>5%
			Interest in smoking or vaping cessation services	Proportion of eligible participants (parents and adolescents) who want to be connected with smoking or vaping cessation services (quit lines, etc)	End of study	Baseline and follow-up questionnaires	>5%
			Interest in obtaining NRT^b^	Proportion of eligible participants in each category who want to receive NRT	End of study	Baseline and follow-up questionnaires	>5%
**Impact on clinic workflow**							
		Clinic staff evaluation		Key informant semistructured interview template (Multimedia Appendix 2) based on a number of references, including the CFIR^c^ interview guide [31] and RE-AIM^d^ [32]	End of study	Key informant interviews	N/A
		Patient flow		Pre- and postrecruitment average weekly and monthly patient volumes in each clinic	End of study	Key informant interviews	<10% change

^a^N/A: not applicable.

^b^NRT: nicotine replacement therapy.

^c^CFIR: Consolidated Framework for Implementation Research.

^d^RE-AIM: Reach, Effectiveness, Adoption, Implementation, and Maintenance.

**Table 2 table2:** Participant-level outcomes of a pilot randomized controlled trial evaluating the feasibility and preliminary effectiveness in Canadian pediatric clinics of a brief digital screening and intervention tool for parental and adolescent tobacco and electronic cigarette use.

Outcome		Operational definition and details of measure	Timeline				Data collection	Feasibility threshold
			Baseline	1 month	3 months	6 months		
**Protocol fidelity**								
	Baseline questionnaire completion	Proportion of participants who complete the baseline questionnaire out of randomized participants (REDCap^a^ survey)	✓				Baseline questionnaire	≥90%
	Access to web-based resources	Proportion of participants who want to be connected to the web-based resources who report access these resources (self-report)	✓	✓	✓	✓	Baseline and follow-up questionnaires	N/A^b^
	Access to quit lines (phone, or SMS text messaging support)	Proportion of interested participants who received a communication from the quit lines (self-report)		✓	✓	✓	Baseline and follow-up questionnaires	N/A
	Access to NRT^c^	Proportion of participants who want to receive NRT who receive a report receiving a formal written recommendation or prescription for NRT	✓	✓	✓	✓	Baseline and follow-up questionnaires	N/A
	NRT use	Proportion of participants who have used NRT (self-report)		✓	✓	✓	Baseline and follow-up questionnaires	N/A
**Study retention**								
	Participant retention	Proportion of randomized participants that could be contacted (initiation of REDCap survey, phone, or email contact) at follow-up		✓	✓	✓	Follow-up questionnaires	≥80%
	Smoking and vaping status	Availability of self-reported smoking and vaping status for randomized participants		✓	✓	✓	Follow-up questionnaires	≥80%
	Completion of data at follow-up	Complete survey data available for randomized participants		✓	✓	✓	Follow-up questionnaires	≥60%
	Cotinine testing	Availability of cotinine testing results		✓	✓	✓	Web-based portal	N/A

^a^REDCap: Research Electronic Data Capture.

^b^N/A: not applicable.

^c^NRT: nicotine replacement therapy.

### Power Calculations

The most recent Statistics Canada data show prevalence rates for daily or occasional smoking that are higher among males (17.3%) than females (12.3%), though this gap is narrowing [33]. In Québec, where the study is conducted, smoking prevalence is slightly higher (17.0%) than the Canadian average (14.8%) [33]. Among adults, especially adults aged older than 25 years, smoking rates remain significantly higher than vaping rates, as only 3.2% of adults aged older than 25 years report past-month use of a vaping device, and a significant proportion of adult e-cigarette users report dual use of cigarettes and vaping devices [34].

The latest provincial statistics report an 18% vaping prevalence among youth aged between 15 and 17 years [35] in Quebec, which is 4.5 times higher than the smoking prevalence (4%) in this age group, though the majority of adolescents who smoke also report past use of an electronic cigarette [34].

Considering recent epidemiological trends, a conservative 15% prevalence estimate is expected for the combined use of cigarettes and vaping devices among both parents and adolescents, resulting in a potential participant pool of approximately 1 in 7 parents or adolescents presenting to the clinic. With average clinic volumes of 250 patients per week and the screening and enrollment rates mentioned above, we anticipate attaining targeted recruitment rates of 3 participants per week.

To estimate the retention rate, using a sample size of 50 participants per age group (parents and adolescents) will allow for a 95% CI within 15% of the estimate obtained. As such, if a study completion rate of 60% is observed, the 95% CI would be 44.2%-75.8%. Other research groups have reported challenges in recruiting teenagers for vaping cessation research studies [36]. As such, recruitment and retention rates are expected to differ between adult and adolescent participants; enrolling 50 parents and 50 adolescents for this pilot study will provide the 2 participation rate estimates.

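### The worked 95% CI for 60% completion (44.2% to 75.8%) is not the interval for 50 participants and is wider than the 15-point precision claimed just before it

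*Protocol article*

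**What the plan says.** The protocol article, Power Calculations, bases the size of each age group on the precision of the retention estimate: "using a sample size of 50 participants per age group (parents and adolescents) will allow for a 95% CI within 15% of the estimate obtained". The next sentence, presented as a consequence, gives the example: "if a study completion rate of 60% is observed, the 95% CI would be 44.2%-75.8"%. The section closes by saying that "enrolling 50 parents and 50 adolescents for this pilot study will provide the 2 participation rate estimates", so each estimate stands on its own group of 50.

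Table 2, under Study retention, defines the completion measure as "Complete survey data available for randomized participants", with a feasibility threshold of at least 60%. The denominator is everyone randomized in the group.

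**The concern.** Two adjacent sentences disagree. The first promises limits no more than 15 points from the estimate. The second gives limits 15.8 points from it. Reading 15% as relative makes this worse, because 15% of 60% is only 9 points.

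The example also does not belong to the sample size it illustrates, since an interval for 50 participants should be narrower. This is the only precision argument offered for 50 per age group; the rest of the section concerns prevalence and recruitment throughput. The article says the trial lacks power to test effectiveness, so precision of estimation is what supports the group size. A reader planning the full-scale trial could reuse the wrong interval, or wonder whether the planned evaluable number was really 50.

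**Working it through.** **Inputs**
- n = 50 per age group, 95% confidence, precision of 15 points (Power Calculations).
- Observed completion p = 0.60, that is 30 of 50; stated interval 44.2% to 75.8% (Power Calculations).
- Denominator: randomized participants (Table 2, Study retention).

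**The plan's own figure**

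The half-width is (75.8 − 44.2)/2 = 15.8 points, and the midpoint is (75.8 + 44.2)/2 = 60.0%. The interval is symmetric about 60%, as a normal-approximation interval would be.

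**Attempt to reproduce it at n = 50**

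The Wald half-width is 1.96 × √(0.6 × 0.4/50) = 1.96 × 0.0693 = 0.136, which gives 46.4% to 73.6%. Other standard methods for 30 of 50:

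| Method | 95% interval | Largest distance from 60% |
|---|---|---|
| Wald | 46.4% to 73.6% | 13.6 points |
| Wald, continuity-corrected (adds 1/(2n) = 0.010) | 45.4% to 74.6% | 14.6 points |
| Wilson | 46.2% to 72.4% | 13.8 points |
| Clopper-Pearson exact | 45.2% to 73.6% | 14.8 points |
| Agresti-Coull | 46.2% to 72.4% | 13.8 points |
| Jeffreys | 46.2% to 72.7% | 13.8 points |

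None gives 44.2% to 75.8%, and all lie within 15 points of 60%. At n = 50 the stated half-width would need z = 0.158/√(0.24/50) = 2.28, about 97.7% confidence. Alternatively it would need a variance inflated by (0.158/0.1358)² ≈ 1.35. The article states neither.

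**Sample size that the stated interval implies**
- Plain Wald: n = 1.96² × 0.24/0.158² = 36.9. Check at n = 37: 1.96 × √(0.24/37) = 0.158, giving 44.2% to 75.8%.
- Continuity-corrected Wald at n = 43: 1.96 × √(0.24/43) + 1/86 = 0.1464 + 0.0116 = 0.158, giving the same limits.
- Other obvious candidates fail under plain Wald: n = 25 gives ±19.2 points and n = 100 gives ±9.6 points.

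**Does the 15-point claim hold at n = 50?**

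Yes. The Wald half-width is largest at 50%: 1.96 × √(0.25/50) = 0.139, or 13.9 points (14.9 with the continuity correction). Computing the exact interval for every count from 0 to 50 gives a largest distance of 14.8 points. By the Wald formula, 15 points needs 1.96² × 0.24/0.15² = 41 participants at 60%, or 1.96² × 0.25/0.15² = 42.7, so 43, at 50%.

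**The case against.** The strongest reply is that the error is harmless. It overstates uncertainty, and the corrected interval supports 50 per group better than the printed one does. The primary outcome is the recruitment rate, and the Discussion ties the case for a full-scale trial to 6 parents and 6 adolescents per month, not to this interval. Results reports 61 parents and 54 adolescents already recruited, so the example can no longer affect the design. All of this stands, and it sets the severity. It does not make the printed interval right.

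A second reply is that the authors may have allowed for attrition. The text gives no reduced number, and completion is measured among those randomized, so dropout does not shrink the denominator.

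Three stronger readings are tempting, and the article supports none of them:
- That the sample size was really 37. This holds only for the plain Wald formula. The continuity-corrected formula gives the same limits at 43, and no method is named.
- That 50 per group is too few for the promised precision. The recalculation shows it is enough.
- That the example should have been set at 80%, the retention threshold. The example concerns study completion, and Table 2 sets the threshold for complete follow-up data at 60%. The 80% thresholds belong to being contactable and to having smoking and vaping status available.

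**Conclusion.** The worked interval is wrong as written, and it contradicts the precision statement before it. Of the two statements, the precision claim is the correct one for n = 50, read as percentage points. The error is about 15.8 − 13.6 = 2.2 points per side against the Wald interval, roughly 16% too wide (15.8/13.6 = 1.16). Its source cannot be identified from the article.

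The conclusion assumes a single proportion, a denominator of 50 randomized participants and two-sided 95% confidence, all as the article states them. Severity is minor: no sample size, threshold, analysis or decision changes.

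**What to change.** In Power Calculations, replace the example interval with the one for 30 of 50 and name the method, for instance the exact (Clopper-Pearson) interval of 45.2% to 73.6%. Keep the precision claim, but word it as 15 percentage points so that it cannot be read as relative.

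If a smaller evaluable number was intended, state that number, its reason and the method, and restate the precision claim to match.

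The cost is one sentence, with no change to design, sample size or analysis.
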